#### Primary analyses

In the primary analysis, 1) changes in the frequency of condomless anal sex from baseline to the 4-, 8-, and 12-month follow-ups and 2) incident STIs from baseline to the 12-month follow-ups between the intervention and control conditions will be compared. Generalized linear models with link functions, selected based on the distribution of the dependent variable, will be used to analyze longitudinal data. To account for repeated measures of the outcome [39], the generalized linear models will be estimated using generalized estimating equations with robust standard error estimates. All statistical tests will determine significance with an alpha level of 0.05. To reduce the threat of bias, the intention-to-treat principle will be utilized, where individuals will be analyzed according to the condition to which they were randomized, regardless of their fidelity to the condition.

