**Methods:**

Funded by the National Institute of Mental Health, this study is a two-arm randomized clinical efficacy trial of a self-acceptance based psychosocial HIV prevention intervention, informed by the minority stress model and syndemic theory, that was developed with extensive community-based formative work and input from the Indian MSM community and key informants who are knowledgeable about the experiences faced by MSM in India. Participants are MSM in Chennai and Mumbai who endorsed recent sexual behaviors placing them at high risk for HIV/sexually transmitted infection (STI) acquisition and transmission. Enrolled participants are equally randomized to either 1) the experimental condition, which consists of four group and six individual counseling sessions and includes standard of care HIV/STI testing and counseling, or 2) the standard of care condition, which includes HIV/STI testing and counseling alone. The primary outcomes are changes in the frequency of condomless anal sex acts and STI incidence (syphilis seropositivity and urethral, rectal, and pharyngeal gonorrhea and chlamydia infection. Major study assessment visits occur at baseline, 4-, 8-, and 12-months.

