#### Randomization

Approximately half of participants are randomized to the psychosocial intervention condition (*N* = ~ 300 across both sites; ~ 150 per study site) and approximately half are randomized to the standard of care control condition (*N* = ~ 300 across both sites; ~ 150 per study site). Random assignments are generated by an interactive web-based response system that can be monitored across study sites. Those randomized to the psychosocial intervention are assigned in order of their randomization into batches of 8 participants for the purpose of doing group intervention sessions together. All batches, except potentially the final batch, are expected to have 8 participants.

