#### Power considerations and sample size calculations

The power analysis for the primary aim is based on detecting a 30% (or greater) difference in 12-month STI incidence and sexual risk (number of unprotected anal sex acts in the past 4 months, baseline to 12-month follow-up) between the intervention and control. Based on this data, with an alpha level of 0.05 and a power of 90%, 480 study completers are needed. Assuming an attrition rate of 20% between the baseline assessment and 12-month follow-up, we need 600 study completers. However, in an attempt to have approximately 8 participants in each batch, our goal is to randomize 608 participants.

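### The primary GEE is described as handling repeated measures only, although the intervention arm is treated in batches of 8; if outcomes correlate within batches, standard errors are too small and 90% power is optimistic

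*Protocol article*

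**What the plan says.** Allocation is equal: the abstract's Methods paragraph has "Enrolled participants are equally randomized to either" of the two conditions. Under Randomization, men allocated to the intervention are "assigned in order of their randomization into batches of 8 participants for the purpose of doing group intervention sessions together", and every batch except possibly the last is planned to be full. Under Psychosocial intervention, each of these men attends four interactive group sessions of about two hours and six one-to-one sessions. The Standard of care section describes testing and counseling, with no grouping of controls.

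The Primary analyses section says of dependence: "To account for repeated measures of the outcome [39], the generalized linear models will be estimated using generalized estimating equations", with robust standard errors. It does not mention batch. The significance rule is "All statistical tests will determine significance with an alpha level of 0.05".

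The power section aims at "detecting a 30% (or greater) difference in 12-month STI incidence and sexual risk" and states that "with an alpha level of 0.05 and a power of 90%, 480 study completers are needed". The allowance for loss reads "Assuming an attrition rate of 20% between the baseline assessment and 12-month follow-up, we need 600 study completers". Batches enter only at the last step: "in an attempt to have approximately 8 participants in each batch, our goal is to randomize 608 participants".

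**The concern.** This is a partially nested design: people are randomized individually, but one arm is then treated in groups. Four sessions of discussion and role-play shared by the same eight men can make their later outcomes more alike than those of men in different batches. A robust variance built on repeated measures within a person allows for correlation within that person and not between batch-mates.

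The gap is clearest for STI incidence. That outcome has a single follow-up measurement, at 12 months, so clustering on repeated measures does essentially nothing for it. The dependence that the design itself creates is the one between batch-mates.

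Both primary comparisons are at stake. If the correlation is positive and ignored, confidence intervals are too narrow, a zero average effect is rejected more often than 5% of the time, and a sample size derived for independent participants delivers less than its stated power.

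**Working it through.** **Inputs from the Protocol article.** Alpha 0.05 (taken as two-sided, since sidedness is not stated); 90% power with 480 completers; 20% attrition; 608 randomized 1:1; batches of 8 in the intervention arm only. The number of batches is 608/2 = 304, and 304/8 = 38. Expected completers per batch are 8 × 0.8 = 6.4.

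**Assumed input.** The batch ICC is not given. The range 0.01 to 0.10 is an assumption.

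**The plan's own figures.** 480/0.8 = 600 reproduces. It is the number to randomize, although the sentence calls these men completers. The 480 itself cannot be checked, because no control STI rate and no mean or dispersion of act counts is given. Read as a 30% relative reduction (two-sided, 90% power), 480 requires a control STI rate of about 48% without continuity correction, or 50% with it. At a 20% rate the same reduction would need 1,644. A standardized difference of 0.296 also gives 480. Below, 480 is taken as the 90% figure for independent participants.

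**Formulas.** Only one arm is clustered, so the design effect applies to half of the variance of the arm difference:

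- Intervention-arm design effect: DE = 1 + (m − 1) × ICC, with m = 6.4.
- Variance ratio of the arm difference: VR = (DE + 1)/2.
- Type I error if batch is ignored: 2 × [1 − Φ(1.960/√VR)].
- Power if batch is accounted for: Φ((1.960 + 1.282)/√VR − 1.960).
- Completers needed to restore 90%: 480 × VR.

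Example at ICC 0.05: DE = 1 + 5.4 × 0.05 = 1.27 and VR = 2.27/2 = 1.135. This gives a type I error of 6.6%, power of 86.1%, and 480 × 1.135 = 545 completers.

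| ICC (assumed) | DE | VR | SE too small by | Type I error, batch ignored | Power, batch accounted for | Completers for 90% |
|---|---|---|---|---|---|---|
| 0.01 | 1.054 | 1.027 | 1.3% | 5.3% | 89.2% | 493 |
| 0.02 | 1.108 | 1.054 | 2.6% | 5.6% | 88.4% | 506 |
| 0.05 | 1.270 | 1.135 | 6.1% | 6.6% | 86.1% | 545 |
| 0.10 | 1.540 | 1.270 | 11.3% | 8.2% | 82.0% | 610 |

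With the 608 × 0.8 = 486 completers actually expected, power is 89.6%, 88.8%, 86.5% and 82.5%.

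**Simulation check.** 20,000 replicates per setting, normal outcome, 38 batches of 6 or 7 completers against 243 unclustered controls, true difference 0.296 SD for power. With a participant-level standard error, type I error was 5.5%, 6.0%, 6.2% and 8.2% across the four ICCs. With a batch-level robust standard error it was 5.4%, 5.4%, 4.9% and 5.4%, and power was 89.7%, 88.6%, 86.3% and 82.2%. These agree with the formulas to within about half a point. The simulation covers a single normal endpoint; skewed act counts and a binary STI outcome were not simulated.

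**The case against.** The strongest reply is that the article does not exclude clustering by batch. It names a purpose (repeated measures) and robust standard errors, but no cluster identifier, and the analysis plan is not shown. That is fair as far as it goes. However, the article does state which dependence the model is there to handle, and that statement leaves out one that its own Randomization section creates. An analyst following the text as written would ignore batch.

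Other parts of the reply stand and limit the point:

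- The size of the harm depends on an unstated ICC. At 0.02 or below, the loss of power is under 2 points. Six of the ten sessions are individual, which may keep the ICC low.
- Because the 480 cannot be reproduced, an unreported allowance for batches cannot be ruled out, although nothing in the section suggests one.
- Similarity that already exists among men enrolled close together is shared with controls enrolled at the same time, so it does not by itself inflate type I error. Only correlation induced by shared treatment does. The type I figures therefore describe a zero average effect with batch effects that are not zero.
- Calculating with 8 per batch gives larger figures (7.1% type I error and 84.9% power at ICC 0.05). Those do not match a power statement about completers.

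A reader might also infer that batch-mates are correlated because they share facilitators or sexual networks. The article does not say how facilitators are assigned to batches, and batches are filled by order of randomization rather than by network, so the point does not rest on either argument.

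**Conclusion.** The point holds in conditional form. The plan treats one arm in batches, describes a primary model that accounts only for repeated measures, and uses batch size in the sample size only to move from 600 to 608. For any positive correlation induced by the group sessions, participant-level standard errors are too small and 90% power is optimistic. Over an assumed ICC of 0.01 to 0.10, type I error is about 5.3% to 8.2% if batch is ignored, and power is about 89% to 82% if it is accounted for. This rests on 6.4 completers per batch, a two-sided test, and 480 being the 90% figure for independent participants.

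A reader might infer that the primary tests are certainly anticonservative or that the trial is certainly underpowered. The document supports neither: it gives no ICC, no inputs from which 480 can be rebuilt, and no explicit cluster identifier. The direction of the problem is clear; its size is not established.

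**What to change.** In Primary analyses, set the GEE cluster to the batch as assigned at randomization for intervention participants and to the individual for controls (clusters of one). Each man's repeated measures lie within his cluster, so the same robust variance covers both sources of dependence. Using the assigned batch keeps the analysis consistent with intention-to-treat. Add a small-sample correction for about 38 batches. A partially nested mixed model should not be substituted as if it were the same analysis: with a logit link for STI it estimates an effect conditional on batch, not the marginal effect that the GEE targets.

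In the power section, restate power over a stated ICC range, applying 1 + (m − 1) × ICC to the intervention arm only, with m as completers per batch. Say whether 480 already contains any such allowance.

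The cost is a change of wording, slightly wider intervals and a slightly lower quoted power, with no extra participants. The assignment procedure implies that batch membership will be available, but this should be confirmed. The clustering unit should be fixed before unblinded outcome data are seen, because choosing it afterwards would be open to challenge.

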##### Primary outcomes

[1] Changes in condomless anal sex measured with self-report using ACASI from baseline to 4-, 8-, and 12-month follow-up assessments. Based on a previous study [32, 33], participants are asked to estimate their number of sexual partners by HIV status, sex, and number of times having anal intercourse with and without a condom in the past 4 months. [2] STI incidence, measured through HIV/STI testing at baseline and the 12-month follow-up assessment. To test for HIV and syphilis, the participant has a small amount of blood drawn. HIV screening is done by rapid card tests using serum or plasma, and syphilis screening is done using serum by the Rapid Plasma Reagin (RPR) assay or the venereal disease research laboratory (VDLR) test. Additionally for syphilis, nonspecific and positive tests (RPR) are confirmed by specific tests (Microhemagglutination Assay for Treponema pallidum Antibodies (MHA-TP) or fluorescent treponemal antibody absorption (FTA-ABS)) and titers of prior tests and treatment histories are obtained in order to ensure that positive results indicate incident infections. To test for chlamydia and gonorrhea, participants provide a small urine sample for testing by nucleic acid amplification testing (NAAT), and a lab employee takes an oropharyngeal sample and a rectal swab using standard assays. All positive cases of STIs are treated on site, and anyone who tests positive for HIV is referred for outside treatment where treatment is provided free of charge.

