#### Secondary analyses

If the psychosocial intervention shows a differential decrease in the frequency of condomless anal sex and/or STI incidence, the extent to which this relationship works through possible mediators, such as self-acceptance, self-esteem, and distress, will be evaluated. Specifically, if a possible mediator is significantly changed by the psychosocial intervention, a mediation analysis will be conducted to determine if the effect of the intervention on the primary outcome was through the possible mediator. A cost-effectiveness analysis, examining the clinical benefits and costs of the psychosocial intervention, in comparison to the clinical benefits and costs of the standard of care control, will also be conducted.

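### Two primary outcomes are each tested at an unadjusted 0.05 with no decision rule, so the overall error is about 10% if either one can support efficacy, and joint power is about 81% if both must

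*Protocol article*

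**What the plan says.** The abstract of the protocol article gives two outcomes equal standing: "The primary outcomes are changes in the frequency of condomless anal sex acts and STI incidence". Study objectives and Primary outcomes number them the same way.

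Primary analyses compares the arms on "changes in the frequency of condomless anal sex from baseline to the 4-, 8-, and 12-month follow-ups" and on "incident STIs from baseline to the 12-month follow-ups". For the method, "the generalized linear models will be estimated using generalized estimating equations with robust standard error estimates". The section does not say which arm contrast from that model is the primary test: an overall arm effect, an arm-by-time test, or a contrast at one visit. On error control it says only: "All statistical tests will determine significance with an alpha level of 0.05".

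Secondary analyses makes the mediation work conditional on whether the intervention "shows a differential decrease in the frequency of condomless anal sex and/or STI incidence".

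Power considerations and sample size calculations sizes the trial on a 30% difference in both outcomes, at an undivided alpha of 0.05 and 90% power. For sexual risk the measure is the "number of unprotected anal sex acts in the past 4 months, baseline to 12-month follow-up". Primary outcomes defines the same outcome as change "from baseline to 4-, 8-, and 12-month follow-up assessments".

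**The concern.** With two primary outcomes, a trial needs a rule that turns two p-values into one conclusion. This article fixes the level of each test but not that rule. The stated 5% and 90% then cannot both describe the overall claim: if one positive outcome is enough, the 5% is too low a figure for the error; if both must be positive, the 90% is generally too high for the power.

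The two outcomes also differ in kind. One is self-reported, by participants who know whether they received counselling; the other rests on laboratory tests. If they disagree, the text gives no basis for deciding whether efficacy was shown. A result on self-report alone could be presented as efficacy while STI incidence shows nothing, and a reader could not tell whether that had been the intended rule.

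For condomless sex there is a second gap. The trial is sized on the 12-month change, but the analysis lists three follow-ups without saying which is confirmatory.

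**Working it through.** **Inputs from the article.** Two primary outcomes; alpha 0.05 for every test; 90% power; 480 completers; 20% attrition; 608 to be randomized. Condomless sex is compared at three follow-ups, STI incidence at one.

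**Assumptions.** Tests are two-sided (sidedness is not stated). The correlations between test statistics are not in the article, so ranges are shown.

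**The plan's own figure.** The attrition step reproduces: 480 / (1 - 0.20) = 600. The 480 cannot be reproduced, because no control STI rate, mean number of acts or standard deviation is given. The stated 90% is taken at face value below.

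**If either outcome is enough.**
- Independent tests: 1 - (1 - 0.05)^2 = 1 - 0.9025 = 0.0975.
- Simulated bivariate normal statistics, correlation 0 to 0.5: about 9.0% to 9.8%.
- Upper limit under any dependence: 2 x 0.05 = 10%.

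**If each visit were also tested separately.** This means three visit contrasts plus STI, any of which could support the claim.
- Independent tests: 1 - 0.95^4 = 1 - 0.8145 = 0.1855.
- Simulated, with correlation 0.3 to 0.7 between visits and 0 to 0.5 between outcomes: about 14% to 18%.

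**If both outcomes are required.**
- The error is at most 5%, because both tests must reject.
- Joint power under independence: 0.90 x 0.90 = 0.81.
- Limits under any dependence: at least 1 - 0.10 - 0.10 = 0.80, at most 0.90.

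**Cost of controlling the error.** An outcome with 90% power at two-sided 0.05 has a standardized effect of 1.9600 + 1.2816 = 3.2415 (unrounded sum).
- Power at 0.025: Phi(3.2415 - 2.2414) = Phi(1.0001) = 0.841.
- Completers needed to keep 90% at 0.025: ((2.2414 + 1.2816) / 3.2415)^2 = 1.181, and 480 x 1.181 = about 567. At 20% attrition that is 567 / 0.80 = about 709 randomized, against 608 planned.

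**Contrast, section against section.** For STI incidence, the power section and the analysis section both use 12 months. For condomless sex, the power section uses baseline to 12 months; the analysis section lists 4, 8 and 12 months. The powered contrast is among those analysed but is not singled out.

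**The case against.** The strongest reply is that the article never says one positive outcome is enough. A reader might infer a success-on-either rule from the and/or wording, but that wording is only the condition for starting a mediation analysis. The power section joins the two outcomes with a plain conjunction, which fits a requirement for both at least as well. This stands: the 10% figure is conditional. It does not remove the problem, because under the other reading the shortfall moves to joint power.

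A reader might also infer that the trial has four chances to claim efficacy, with an error near 18%. The article does not support that as a finding. It describes a repeated-measures model, which can yield one overall or arm-by-time test for condomless sex and so bring the count back to two. The 14-18% range applies only to separate visit tests and rests on assumed correlations.

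A third tempting reading is that the powered contrast is not the one analysed. That is wrong for STI incidence. For condomless sex it goes too far, since the 12-month change is within the analysis, and sizing on one visit while fitting a longitudinal model is ordinary practice.

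Finally, this is a condensed article, and a statistical analysis plan that is not shown may set the contrast and a multiplicity procedure. Silence on those details is not held against it. The criticism rests on what the article does fix: 0.05 for all tests, and an undivided 0.05 in the sample size. A later multiplicity rule would have to override the first statement and would change the meaning of the second.

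**Conclusion.** The point holds in a limited form. Two primary outcomes are tested at an unadjusted 0.05, and the article does not say how they combine.

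- If either can support efficacy, the family-wise error is about 10%, twice the stated level. This hardly depends on the correlation: 9.0-9.8% over the range assumed.
- If separate visit tests could also support the claim, the error is roughly 14-18%. The text leaves this possibility open but does not prescribe it.
- If both outcomes are required, the error is controlled and joint power is about 81% under independence.

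The powered-versus-analysed gap concerns condomless sex only and amounts to not naming the 12-month contrast as confirmatory. All power figures assume that the stated 90% is correct for each outcome, which the article does not allow a reader to verify.

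**What to change.** In Primary analyses, replace the blanket 0.05 for the two primary outcomes with Holm or Hochberg at a family-wise 0.05, and say that efficacy means at least one rejection under that procedure. Name the 12-month arm contrast from the longitudinal GEE model as the confirmatory test for condomless sex, and report 4 and 8 months as secondary. In Secondary analyses, tie the and/or condition to the same rule. A fixed hierarchy or a both-must-succeed rule would also control the error. If both are meant to be required, the article should say so and give the joint power.

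No new data or visits are needed, and no added enrolment is proposed. The price is power: at the strictest step (0.025), an outcome with 90% power at 0.05 has about 84%, and the power section should report that figure beside the 90%. Under Holm, the second outcome is tested at the full 0.05 once the first has been rejected. Holm is valid under any dependence between the outcomes; Hochberg needs independence or a form of positive dependence, which should be stated if it is chosen.

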#### Secondary analyses

If the psychosocial intervention shows a differential decrease in the frequency of condomless anal sex and/or STI incidence, the extent to which this relationship works through possible mediators, such as self-acceptance, self-esteem, and distress, will be evaluated. Specifically, if a possible mediator is significantly changed by the psychosocial intervention, a mediation analysis will be conducted to determine if the effect of the intervention on the primary outcome was through the possible mediator. A cost-effectiveness analysis, examining the clinical benefits and costs of the psychosocial intervention, in comparison to the clinical benefits and costs of the standard of care control, will also be conducted.

